**Statistical analysis and outcome measures**

The primary end point of the study will be development of tuberculosis and the secondary endpoints will include adverse drug reactions and mortality rate. The intention-to-treat approach will be used for analyzing the data for primary and secondary end points. Annual interim analyses will be done to ensure timely identification of any significant risks or benefits to patients. The treatment groups will be compared to note random distribution of baseline demographic and socio-economic, clinical and laboratory characteristics. The incidence of tuberculosis will be estimated by the person-year method. Cumulative proportion will be used for adverse reactions and mortality. The log rank test of significance will be used to compare cumulative incidence of TB in the treatment groups. Survival analyses using the log rank testing the null hypothesis and Kaplan Meier curves for depicting cumulative survival in TB and mortality will be done to compare outcomes between study groups. Multivariate analyses will be performed using Cox’s proportional Hazards model.

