**Study Design**

The study will be a two-armed prospective randomized clinical trial among HIV- positive patients without active tuberculosis. Enrolled patients will be assigned to one of the two unsupervised self-administered treatment regimens i.e. EH for 6 months or INH alone for 3 years. At the end of a 3-year follow-up, incidence of TB and overall mortality will be compared in each group.

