**Sample Size**

Assuming that prophylaxis will result in reduction of the incidence of TB in HIV positive persons from 7/100 person years (published TRC study) to 3/100 person years, the sample size for each arm is calculated to be 250. Allowing for a 10% drop out rate per year due to death or default, the number of patients required per treatment arm will be 325.

Total number of patients to be admitted to the study: 650

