# The treatment regimens in each study group will be as follows:

1. Ethambutol (800 mg) and Isoniazid (300 mg) daily for six months, self-administered, collected once in fifteen days.
2. Isoniazid (300 mg) daily for 3 years (in lieu of lifelong prophylaxis) with fortnightly collection of drugs

Subjects in both study groups will receive 10 mg of Pyridoxine daily during treatment.

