**Follow-up**

During chemoprophylaxis

All enrolled patients will be followed up regularly to monitor general clinical status, adverse effects, adherence to drugs and development of active tuberculosis. Patients will be called to the clinic three monthly for a thorough clinical assessment and measurement of weight (see table). During each clinic visit, patients will be verbally screened for chest symptoms. In the presence of chest symptoms, the patient will be thoroughly evaluated clinically, and investigated for tuberculosis by radiological examination and 3 sputum specimens for smear and culture.

During each follow up visit the patient will asked for any symptoms or signs of drug toxicity. Details of any adverse reactions and their management will be recorded on a standardized toxicity form. Adverse reactions will be appropriately managed.

Adherence to the assigned regimen will be checked by detailed questioning of patients, return of empty drug packs, and by examination of spot urine samples for acetyl isoniazid. Non-adherent patients will be counseled regarding importance of treatment regularity and monitored closely. If a patient fails to attend the on the due date for drug collection, a letter will be posted, following which a health visitor or social worker will visit his/her home in case there is no response within a week.

Post Chemoprophylaxis

Patients will be followed up for a period of three years from the time of admission to the study. Clinical examination and relevant investigations will be done 3 monthly. Patients suspected to have tuberculosis at any time will be fully investigated and treated appropriately. Any positive culture will be subjected to drug susceptibility tests. If a patient dies, a verbal autopsy will be conducted to ascertain the cause of death**.**

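### The cumulative proportion is the only measure named for adverse drug reactions, although the arms take drug for 6 v 36 months; alone it cannot separate tolerability from duration

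*Protocol*

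**What the plan says.** Under *Statistical analysis and outcome measures*, TB is the primary endpoint; adverse drug reactions and the mortality rate are secondary. All are to be analysed by intention to treat. The section assigns the person-year method to TB incidence and then states: "Cumulative proportion will be used for adverse reactions and mortality". The survival-analysis sentence plans log-rank tests and "Kaplan Meier curves for depicting cumulative survival in TB and mortality", followed by Cox models. It names TB and mortality but not adverse reactions. Annual interim analyses are to look for risks and benefits.

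The regimens are "Ethambutol (800 mg) and Isoniazid (300 mg) daily for six months, self-administered, collected once in fifteen days" and "Isoniazid (300 mg) daily for 3 years (in lieu of lifelong prophylaxis) with fortnightly collection of drugs". Follow-up is the same length in both arms: "Patients will be followed up for a period of three years from the time of admission to the study".

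In the *Follow-up* section, the instruction to ask about toxicity at each visit and to complete a toxicity form stands under the sub-heading for the period during chemoprophylaxis. The text for the period afterwards keeps three-monthly clinical examination but does not repeat that instruction.

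**The concern.** Time on drug differs six-fold by design, and so, as written, does the period of structured toxicity enquiry. After month 6 the reaction comparison is drug against no drug. One proportion at 36 months therefore mixes two questions: how well each regimen is tolerated while taken, and how much toxicity accrues because one regimen lasts longer.

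The Introduction itself raises the possibility that shorter regimens carry more toxicity. If the two-drug regimen were harder to tolerate month for month, a single 36-month proportion could hide it. The annual interim reviews have the same difficulty. For patients followed 12, 24 and 36 months, assigned time on drug is 6 v 12, 6 v 24 and 6 v 36 months, so the isoniazid proportion can move away from the other arm's with no change in monthly toxicity.

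At stake is the reading of a named secondary endpoint. The primary TB comparison is not affected.

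**Working it through.** The protocol gives no expected reaction or death rate, so there is no figure of its own to reproduce on this point. All event rates below are assumptions.

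**Inputs from the protocol**
- Time on drug: 6 months v 36 months (treatment regimens).
- Follow-up: 36 months in both arms (*Follow-up*).
- Patients: 325 per arm, which is 250 × 1.30 (*Sample Size*).
- Attrition: 10% per year, deaths included (*Sample Size*).

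**1. Constant hazard on drug, no loss.** Proportion with a reaction = 1 − exp(−m × months on drug).
- m = 0.5% per month in both arms: 1 − exp(−0.03) = 3.0% v 1 − exp(−0.18) = 16.5%.
- m = 1% per month in both arms: 1 − exp(−0.06) = 5.8% v 1 − exp(−0.36) = 30.2%.
- m = 2% (two-drug arm) v 0.5% (isoniazid): 1 − exp(−0.12) = 11.3% v 16.5% at 36 months. Over months 0–6 alone, the same rates give 11.3% v 3.0%.

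**2. Constant hazard with loss.** With loss hazard d = −ln(0.9) = 0.105 per year and reaction hazard r per year, the observed proportion is r/(r + d) × (1 − exp(−(r + d)T)), with T = 0.5 or 3 years. Equal hazards in both arms give:

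| r per 100 person-years | T = 0.5 | T = 3 | Ratio |
|---|---|---|---|
| 2 | 1.0% | 5.0% | 5.2 |
| 5 | 2.4% | 12.0% | 5.0 |
| 10 | 4.7% | 22.4% | 4.7 |
| 20 | 9.3% | 39.3% | 4.2 |

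With 325 per arm and a two-sided 5% test (assumed; the protocol states no level), the chance of a significant difference is 86% at 2 per 100 person-years and over 99% from 5 per 100. The on-drug rate ratio is 1 throughout.

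**3. All reactions in the first 6 months.** If a share p of each arm reacts by month 6 and nobody later, the 6-month and 36-month proportions are both p in both arms. There is no duration effect. An overall rate per person-time on drug then misleads in the other direction:
- Time on drug without loss is 325 × 0.5 = 162.5 v 325 × 3 = 975 person-years, so isoniazid looks 975/162.5 = 6.0 times safer.
- With 10% loss per year it is about 158 v 836 person-years, a factor of 836/158 = 5.3.

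**4. Mortality.** At an assumed 5 deaths per 100 person-years, the 3-year Kaplan-Meier risk is 1 − exp(−0.15) = 13.9%. Deaths divided by patients randomised would give:
- 12.9% if the 10% per year includes deaths, as the protocol says: 0.05/0.105 × (1 − 0.9³).
- 12.0% if 10% loss came on top of deaths: 0.05/0.155 × (1 − exp(−0.466)).

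For 1 to 7 deaths per 100 person-years the relative shortfall is 5% to 13% in the first case and about 14% in the second. This matters only if the reported proportion is that crude one.

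**The case against.** The strongest reply is that duration is part of each intervention. Follow-up is equal and intention to treat applies to secondary endpoints, so the 36-month proportion correctly answers which strategy gives more patients a reaction. That stands. It is why the figure should be kept, and why 11.3% v 16.5% is not an error in itself.

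It can also be said that on-drug rates and common time windows are often left to an analysis plan, which is not at hand. This has some force. But the protocol does not leave the measure open: it names one for adverse reactions, and the adjacent sentences give time-based methods to TB and mortality only.

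Two stronger readings are tempting, and the document supports neither.
- A reader might infer that the toxicity comparison mainly measures duration, or will reverse the ranking of the regimens. Both follow only if reactions continue over time on drug at rates like those assumed; the protocol gives no rates.
- A reader might infer that reported mortality will be too low, or biased between arms by unequal default. But the same section plans Kaplan-Meier, log-rank and Cox analyses for mortality and never defines the cumulative proportion as deaths over patients randomised. The attrition allowance reads "Allowing for a 10% drop out rate per year due to death or default", so it is not all censoring. A between-arm distortion also needs unequal default. An assumed 3% v 10% per year yields 1.2 to 1.9 points, against a standard error of about 2.6 to 3.1 points with 325 per arm, and the protocol says nothing to support that split.

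**Conclusion.** The point holds for adverse reactions, as a limitation of a measure that stands alone and not as an invalid analysis. The 36-month cumulative proportion is sound for comparing strategies but cannot separate tolerability from duration when the arms take drug for 6 v 36 months and structured toxicity enquiry is described only on drug.

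The size depends on when reactions occur. Under an assumed constant and equal hazard, the longer arm's proportion is 4.2 to 5.2 times higher with the planned attrition (3.0% v 16.5% at 0.5% per month without loss). With all reactions in the first 6 months, the effect is nil. The truth may lie anywhere between, and a month-6 comparison is informative in either case.

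For mortality, only a wording ambiguity remains: the endpoint is called a rate, the summary a cumulative proportion, and the comparison is by Kaplan-Meier and log-rank.

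**What to change.** Amend the sentence on adverse reactions to report, by arm:
- the cumulative proportion with a first reaction by month 6, when both arms are assigned drug, as the tolerability comparison;
- the 36-month cumulative proportion, labelled as the whole-strategy figure;
- optionally, the first-reaction rate per person-time on drug, split at month 6 so that early reactions are not diluted by the later isoniazid time.

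Use the same layout at the annual interim analyses. For mortality, add one clause saying that the cumulative proportion is the Kaplan-Meier estimate, and leave the planned log-rank and Cox analyses as they are.

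The cost is a reworded sentence and a few extra table rows, with two toxicity figures (three with the optional rate) to present instead of one. It must also be confirmed that the toxicity form captures the date of each reaction and, if the rate is used, that the date of stopping drug is recorded. The protocol says that details of reactions and their management are recorded but does not mention dates.

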Preventive therapy (PT) against TB is the use of one or more anti-tuberculosis drugs given to patients with latent infection with *Mycobacterium tuberculosis* in order to prevent the progression to active disease. HIV is the major cause of the large increase over the last decade in the incidence of tuberculosis in populations with a high prevalence of HIV infection. Several studies have now demonstrated that PT is effective in preventing TB in individuals dually infected with HIV and *M. tuberculosis*. Studies conducted in USA, Africa and Haiti indicate that preventive therapy is efficacious in HIV positive persons with tuberculin reactions > 5mm, and that the optimal duration of isoniazid preventive therapy (using a single drug) should be greater than six months to provide the maximum degree of protection. Recently, a two-month regimen of daily rifampicin and pyrazinamide was found to provide protection equivalent to daily isoniazid for one year. The advantage of shorter regimens is better patient compliance and possibly earlier sterilization of lesions; however, the risk of drug toxicity maybe higher. The efficacy of preventive therapy in Mantoux negative HIV+ persons has not been clearly established, most studies showing it to be of limited value. Results of prevention trials conducted around the world are summarized in Annex 2.

Although there is large body of literature indicating benefit from preventive therapy, particularly among Mantoux Test (MT) positive persons, several issues regarding preventive therapy for tuberculosis in HIV positive persons need to be addressed in the endemic Indian setting. Due to the continuous environmental exposure to mycobacteria in the Indian setting, it is likely that HIV positive persons are at increased risk for disease due to both re-activation and re-infection. Hence, HIV positive persons who are Mantoux negative could also be at a high risk for developing tuberculosis following primary infection. In this setting, there is need to evaluate the efficacy of prophylaxis for tuberculosis in both tuberculin positive and negative individuals. The duration of preventive therapy required in an endemic setting is another areas requiring further investigation. Currently, preventive therapy is not included as part of the RNTCP. However, the growing problem of HIV in India could make prevention of tuberculosis in this high-risk group a priority area in the years to come.

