**Study Objective**

To compare the efficacy of two TB preventive therapy regimens in reducing the incidence of tuberculosis and mortality among HIV-infected persons.

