**Randomization and Dosing**

All patients enrolled in the prevention trial will be randomized to one of the study groups using a permuted block randomization scheme of four. Stratification will be done by Mantoux reading (>5mm and ≤5mm). The group assignment list will be generated centrally before the start of trial and sequentially numbered sealed envelopes containing the study group assigned will be prepared independently. At the initiation of prophylaxis, each patient will be counseled about the importance of taking drugs regularly. Patients will be asked to return the empty packets as well as unused tablets at each monthly visit.

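### Randomisation is stratified by Mantoux reading, but the log-rank test named for the primary endpoint does not carry that factor; stratifying it is a small improvement at almost no cost

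*Protocol*

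**What the plan says.** Under Randomization and Dosing, the protocol uses a "permuted block randomization scheme of four" and names one stratification factor: "Stratification will be done by Mantoux reading (>5mm and ≤5mm". No other factor enters the allocation.

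Under Statistical analysis and outcome measures, the primary endpoint is fixed ("The primary end point of the study will be development of tuberculosis") and so is its test: "The log rank test of significance will be used to compare cumulative incidence of TB in the treatment groups". The section adds Kaplan-Meier curves and a Cox model: "Multivariate analyses will be performed using Cox’s proportional Hazards model". It does not mention Mantoux or strata. It does not call the log-rank test unstratified, and it lists no covariates for the Cox model.

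The introduction gives background on tuberculin status. It reports that preventive therapy works in reactors above 5 mm and is of unclear value in Mantoux-negative persons, and it says that "there is need to evaluate the efficacy of prophylaxis for tuberculosis in both tuberculin positive and negative individuals". The Study Objective does not mention Mantoux: "To compare the efficacy of two TB preventive therapy regimens in reducing the incidence of tuberculosis and mortality among HIV-infected persons".

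**The concern.** A stratified randomisation balances the arms within each stratum. If the factor predicts the outcome, this removes part of the chance variation in the treatment comparison. An ordinary log-rank test does not know this: its variance still contains the between-stratum part, so the test statistic is a little too small. A stratified log-rank test uses the variance that the design produces.

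What is at stake is some power, and a choice between two tests that is better settled before the data are seen. The validity of a positive finding is not at stake, because the error goes only in the conservative direction.

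**Working it through.** **Inputs from the protocol.** 650 patients, 325 per arm; blocks of four within two Mantoux strata; 3 years of follow-up; 10% loss per year; TB rates of 7 and 3 per 100 person-years, so a hazard ratio of 3/7 ≈ 0.43.

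**Assumed, because the protocol gives no figure.** Two-sided 5% level; Mantoux-positive share 30% or 50%; TB rate ratio, Mantoux-positive to Mantoux-negative, of 1, 2, 4 or 8 with the overall average rate held fixed; exponential event and loss times.

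**The plan's own sample size.** 250 × 1.30 = 325, so the dropout allowance reproduces. The figure of 250 cannot be derived uniquely, since level, power and horizon are not stated in this document. One reading comes close: 3-year risks 1 − exp(−0.21) = 0.189 and 1 − exp(−0.09) = 0.086, two-sided 5%, 90% power and continuity correction give 251. Nothing below depends on this.

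**Check of the simulation set-up.** With loss hazard δ = −ln 0.9 = 0.105, the expected events per patient at TB rate λ are λ/(λ+δ) × [1 − exp(−3(λ+δ))]. This is 0.163 at λ = 0.07 and 0.074 at λ = 0.03. Expected events are then 325 × 0.163 + 325 × 0.074 ≈ 53 + 24 = 77, and the simulation averaged 77.1. The events formula gives √77/2 × |ln(3/7)| − 1.96 = 3.72 − 1.96 = 1.76, or about 96% power. Simulated power with no Mantoux effect and 50% positive was 95.05% (ordinary) and 95.15% (stratified).

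**Closed-form check of the conservatism (50% positive, ratio 4, both arms at 7 per 100).**
- Stratum rates are 0.028 and 0.112, which average 0.07.
- Expected events are 22.5 and 80.2, total 102.7 (simulated: 102.7).
- Person-years are 22.5/0.028 = 804 and 80.2/0.112 = 716, total 1,520, so the pooled rate is 102.7/1,520 = 0.0676.
- Events expected at the pooled rate are 54.3 and 48.4. Each stratum departs by 31.8.
- The variance share removed by stratified allocation is about 2 × (31.8²/325)/102.7 = 6.2/102.7 ≈ 0.06.
- The effective critical value is 1.96/√0.94 ≈ 2.02, so true size is about 4.3%. The simulation gave 4.23%.

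**Simulation results** (10,000 trials under the null, at 7 and at 3 per 100; 4,000 at 7 versus 3). Ranges run over the assumed shares and null rates.

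| Rate ratio | Size, ordinary | Power, ordinary | Power, stratified | Power lost |
|---|---|---|---|---|
| 2 | 4.8–5.0% | 94.0–94.1% | 94.3–94.5% | about 0.3 points |
| 4 | 4.1–4.8% | 93.6–93.8% | 94.4–94.6% | under 1 point |
| 8 | 3.7–4.6% | 91.1–92.3% | 93.3–93.6% | 1–2.5 points |

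The stratified test had size 4.9–5.6% throughout. Monte Carlo standard error is about 0.2 points for size and 0.3–0.5 points for power.

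**A smaller difference.** The Sample Size section describes 7 to 3 as the reduction due to prophylaxis, yet both arms receive prophylaxis. A smaller gap between arms is therefore worth examining. At an assumed 5 versus 3 per 100 person-years with 40% Mantoux-positive, two separate sets of simulations gave:
- ratio 2 (one set only): 50.4% ordinary versus 50.9% stratified;
- ratio 4: 48.6–48.9% versus 50.8–51.2%, a loss of 2.2–2.3 points;
- ratio 6: 47.0–47.2% versus 50.2–50.4%, a loss of 3.0–3.4 points.

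**The case against.** The strongest objection is that this argues from silence. The protocol does not say the log-rank test is unstratified, and such detail often sits in a statistical analysis plan, which is not at hand. That limits the point but does not remove it. The protocol names its primary test and leaves out the only factor it randomises by, and a better-matched test is available for one added sentence.

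The objection does defeat three stronger readings.

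- *The Cox model omits Mantoux.* A reader might infer this, but the model is described as multivariate with no covariates listed. Mantoux may well be among them.
- *The test is materially mis-calibrated.* The error is only conservative and is negligible at a twofold rate ratio. The fourfold and larger ratios have no support in the protocol, which gives no reason for choosing the stratification factor and argues that Mantoux-negative persons in this setting could also be at high risk.
- *The question that motivates the trial goes unanswered.* Efficacy by tuberculin status is background in the introduction, not an objective. With two active arms and no untreated arm, no analysis of this trial could show whether prophylaxis works in Mantoux-negative persons.

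It is also fair to say that a stratified hazard ratio is not a less biased version of the marginal one. The two are different estimands. The gap here is very small: a marginal hazard ratio of 0.60–0.62 against a stratum-specific 0.60.

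**Conclusion.** The point holds as a minor one. The primary log-rank test, as named, does not use the factor that structures the randomisation. If it is run as an ordinary test and Mantoux status is prognostic, it is slightly conservative. At the protocol's own rates the power loss stays under 1 point up to a fourfold rate ratio and reaches 1–2.5 points only at eightfold. At an assumed 5 versus 3 per 100 person-years, where power is near one half, it is about 2–3 points at ratios 4 to 6. If Mantoux is not prognostic, the two tests perform alike. All these figures rest on assumed Mantoux shares and rate ratios. A significant result from the ordinary test would remain valid.

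**What to change.** In Statistical analysis and outcome measures, state that the primary log-rank test for tuberculosis is stratified by the Mantoux reading used at randomisation (>5 mm, ≤5 mm). Take the hazard ratio and its 95% confidence interval from a Cox model stratified by, or adjusted for, the same factor, and say that this is a stratum-conditional estimate. Specify the month-0 reading, because the schedule also repeats the test when tuberculosis is diagnosed.

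TB rates and hazard ratios within each stratum can be added as supportive results. They should be labelled as comparisons of the two regimens only, not as evidence on prophylaxis against no treatment.

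The cost is a sentence or two. No new data are needed, and with only two strata the loss of power is essentially nil. The one consequence to acknowledge is the move from a marginal to a conditional hazard ratio.

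### Kaplan-Meier curves for tuberculosis with death as a competing event: any 36-month TB risk read from them would be modestly too high, and the log-rank compares TB hazards, not cumulative incidence

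*Protocol*

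**What the plan says.** The Statistical analysis section of the protocol makes TB the primary endpoint and places mortality among the secondary endpoints. For TB it names four tools:

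- an incidence rate by the person-year method;
- a log-rank test, described thus: "The log rank test of significance will be used to compare cumulative incidence of TB in the treatment groups";
- "Kaplan Meier curves for depicting cumulative survival in TB and mortality";
- a Cox model for multivariate analysis.

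Mortality is also to be summarised as a cumulative proportion.

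Three other places bear on death. The Study Objective compares the regimens "in reducing the incidence of tuberculosis and mortality among HIV-infected persons", so a mortality difference between arms is contemplated. The Sample Size section inflates the numbers with the words "Allowing for a 10% drop out rate per year due to death or default", which pools death with default. The Follow-up section provides for a verbal autopsy when a patient dies.

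The protocol gives no rule for a patient who dies without TB in the TB curve, and it does not mention competing risks.

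**The concern.** Patients are HIV-infected and, under the enrolment criteria, not on antiretrovirals at entry. Some will die before TB develops. With TB as the sole primary event and mortality analysed separately, an ordinary Kaplan-Meier curve for TB can only place such a death among the censored observations. One minus that curve then estimates the TB risk in a hypothetical population in which nobody dies, not the proportion of patients who develop TB.

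The description of the log-rank has a related fault. With competing deaths the test compares cause-specific TB hazards. Two arms can have equal TB hazards and different cumulative incidences if their mortality differs.

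What is at stake is the absolute scale. The Study Design section sets the comparison at the end of three years. If 36-month risks are read from the curves to weigh six months of treatment against three years, they will be somewhat too high, by an amount that depends on mortality in each arm.

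**Working it through.** **Inputs**

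- TB rates: 0.07 and 0.03 per person-year, from the Sample Size section: "reduction of the incidence of TB in HIV positive persons from 7/100 person years (published TRC study) to 3/100 person years". They are stated there as rates without and with prophylaxis, whereas both trial arms receive prophylaxis. They serve here only as illustrative TB hazards.
- Follow-up: 3 years (Follow-up section).
- Death rate before TB: not given. I assume 1 to 10.5 per 100 person-years. The top value takes all of the 10% yearly loss as death: −ln(0.9) = 0.1054.
- Hazards are assumed constant.

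**The plan's own figure.** The protocol states no 3-year TB risk. The only figure to reproduce is that "the sample size for each arm is calculated to be 250". The 3-year risks without competing death are 1 − exp(−0.21) = 18.94% and 1 − exp(−0.09) = 8.61%. Comparing these two proportions at two-sided 5% and 90% power gives 232 per arm, or 251 with continuity correction. Alpha and power are not stated, so this match is not unique. The 325 per arm is 250 × 1.30. Neither number is affected by the point made here.

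**Formulas for TB hazard h and death hazard d**

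- One minus Kaplan-Meier, deaths censored: 1 − exp(−3h)
- Cumulative incidence, death competing: h/(h + d) × [1 − exp(−3(h + d))]

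Example with h = 0.07 and d = 0.05: 0.07/0.12 × [1 − exp(−0.36)] = 0.5833 × 0.3023 = 17.64%, against 18.94% by Kaplan-Meier.

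**Same death rate in both arms** (Kaplan-Meier gives 18.94%, 8.61% and a difference of 10.33 points throughout; excesses are from unrounded values)

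| Deaths per 100 PY | Cumulative incidence, h = 0.07 | Excess of 1 − KM | Cumulative incidence, h = 0.03 | Excess of 1 − KM | True difference |
|---|---|---|---|---|---|
| 1 | 18.67% | 0.27 | 8.48% | 0.13 | 10.19 |
| 3 | 18.14% | 0.80 | 8.24% | 0.37 | 9.91 |
| 5 | 17.64% | 1.31 | 8.00% | 0.61 | 9.63 |
| 8 | 16.91% | 2.03 | 7.67% | 0.94 | 9.24 |
| 10.5 | 16.33% | 2.61 | 7.40% | 1.21 | 8.93 |

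The excess is 0.1 to 2.6 points, or about 1.5% to 16% in relative terms. The risk ratio hardly moves: 0.454 by Kaplan-Meier against 0.453 to 0.454.

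**Different death rates by arm** (assumed, for direction only)

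- Deaths of 8 in the arm with h = 0.07 and 3 in the arm with h = 0.03: true difference 16.91 − 8.24 = 8.7 points, against 10.3 by Kaplan-Meier.
- Deaths of 3 and 8, the reverse: 18.14 − 7.67 = 10.5 points (unrounded inputs), against 10.3.
- Equal TB hazards of 0.05, deaths of 8 and 3: Kaplan-Meier shows 1 − exp(−0.15) = 13.9% in both arms. The actual risks are 0.05/0.13 × [1 − exp(−0.39)] = 12.4% and 0.05/0.08 × [1 − exp(−0.24)] = 13.3%.

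The last case shows why a log-rank test is not a test of cumulative incidence: the TB hazards are identical, yet the cumulative incidences differ.

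**The case against.** The strongest reply is that the protocol never says deaths are censored in the TB curve and never undertakes to report a 3-year TB risk or risk difference. Its stated estimator of incidence is the person-year rate. With follow-up ending at death, that is a valid cause-specific rate, free of this bias. Kaplan-Meier is named only for display, and the planned wording could be read as one combined TB-free survival curve. The handling of death might also be set in a statistical analysis plan that is not shown.

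Much of this stands. A reader might infer that the protocol prescribes censoring at death, or that the trial's reported TB incidence will be biased. The text supports neither: the first is an inference and the second ignores the person-year method. A reader might also infer that the primary test is invalid. It is not, because a comparison of TB hazards is a reasonable target for a preventive drug. Nor can it be said that the risk difference is always inflated; the reversed death rates above show the opposite.

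The effect is also modest. With 325 per arm and no losses, the 95% half-width for the difference is 1.96 × √[(0.1894 × 0.8106 + 0.0861 × 0.9139)/325] ≈ 5.2 points. The 8-versus-3 death contrast has no support in the protocol.

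What does not fall away is the text itself. The log-rank is assigned to a quantity it does not test. A Kaplan-Meier curve for TB either censors deaths or, if combined with death, no longer depicts the primary endpoint. Both faults lie in what the protocol states, not in what it leaves to a later plan.

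**Conclusion.** The point holds in a limited form. If deaths are censored in the TB curve, which is the natural reading, any 36-month TB risk read from it overstates the actual risk in each arm by about 0.1 to 2.6 points. This range rests on constant hazards, the planning rates of 7 and 3 per 100 person-years, and assumed death rates of 1 to 10.5 per 100 person-years. With equal mortality the risk ratio is almost unchanged and the difference falls from 10.3 to between 10.2 and 8.9 points. With unequal mortality the difference may be off in either direction. The description of the log-rank is wrong whatever the death rate, but its use is sound. The person-year rates, the log-rank and Cox comparisons of TB hazards, and the sample size are unaffected. This is an inexpensive improvement to presentation and wording, not a defect in the primary test.

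**What to change.** In the Statistical analysis section of the protocol:

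- Show the TB curves, and any 36-month TB risk or risk difference with its interval, by the cumulative incidence function (Aalen-Johansen), with death without TB as a competing event. Default remains censored.
- Describe the log-rank and Cox analyses of TB as comparisons of TB hazards.
- Keep the person-year rates for TB and keep Kaplan-Meier for all-cause mortality.

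This takes two or three sentences, uses standard software and data already to be collected, and changes neither the primary test nor the sample size. The cost is slightly lower stated TB risks and a little more analysis work.
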